### Recruitment {15}

Participants will be recruited at Shanghai Stomatological Hospital, Shanghai Ninth People’s Hospital affiliated to Shanghai Jiao Tong University, and Shanghai Children’s Hospital, all of which are located in Shanghai, China, from May 2018 to December 2021 (anticipated). These hospitals comprise all diagnostic and treatment departments, including ear, nose, and throat and stomatological departments. Notification of subject recruitment will be published in these three hospitals and on their official websites.

## Assignment of interventions: allocation

### Sequence generation {16a}

A Central Randomization System was designed with the help of Shanghai KNOWLANDS MedPharm Consulting Co., Ltd., and then installed in researchers’ phones in every study site.

### Concealment mechanism {16b}

The Central Randomization System can be used for the management of participant information and randomization. Prior to signing an informed consent form, this study will be fully explained to subjects and their guardians by researchers at every study site. The basic information of patients will be registered into the Central Randomization System by research assistants. After the baseline survey, the eligible participants will be divided into four groups at random with a ratio of 1:1:1:1.

### Implementation {16c}

Randomization will be implemented by a data analyst from Shanghai KNOWLANDS MedPharm Consulting Co., Ltd., using the minimization method with 80% allocation probability according to the following stratification factors: (1) male/female patient; (2) obese or not based on BMI. Then an email will be submitted automatically to the project coordinator with the ID numbers and groups of participants to be randomized. The project coordinator will then contact participants to inform them about the initiation of treatment.

## Assignment of interventions: blinding

### Who will be blinded? {17a}

When analyzing the outcomes, the analyst will be blinded to the patients’ information during the measurements.

### Procedure for unblinding if needed {17b}

This item is not applicable. The analysts are not allowed to be unblinded under any circumstances.

## Data collection and management

### Plans for assessment and collection of outcomes {18a}

Case report forms (CRFs) specially designed by coordinator investigators and Shanghai KNOWLANDS MedPharm Consulting Co., Ltd. are used for documentation. The training related to recruitment, screening, randomization, evaluation, and instructions for CRF will be organized before the study for the researchers in order to enable conduction of a high-quality clinical trial. A CRF must be filled out for every subject by investigators. All data and information in the CRF must be clear. Changes in the CRF must be marked with a line across the incorrect data. Both incorrect data and the corrections must be kept legible, and the signature of the researcher and time of correction must be marked next to corrected data. A qualified clinical research assistant who is blinded to the patients’ group will supervise the study process at a fixed period, including the completion of informed consent, the screening process, the intervention treatment, the recording of adverse events, and the filling out of the CRF. The original CRFs will be used by the data management center and then returned to the sponsor center, Shanghai Stomatological Hospital.

### Plans to promote participant retention and complete follow-up {18b}

Clinical research assistants from every study site will contact participants monthly to promote their retention and complete their follow-up. Additional services will be provided for participants through WeChat or phone to arrange treatment times to enhance adherence.

### Data management {19}

The original CRFs will be used by the data management center and then returned to the sponsor center, Shanghai Stomatological Hospital. All the questionnaires, PSG data, and image measurement data will be collected, stored in separate folders, and regularly checked. The outcomes will be encoded and entered in a timely manner using EpiData 3.1 double-entry test results.

### Confidentiality {27}

Subjects will be informed that their data will be stored and analyzed on a computer, but that only the research team members can obtain the information associated with each subject. In addition, subjects will be informed of the possibility that their clinical records will be reviewed by representatives of the sponsor and/or regulatory authority. All unpublished information, including patent applications, production processes, and basic data, will be deemed confidential. Any public report of the results of this study will not disclose the personal identity of the participants. The trial data will be available for public inquiry and sharing, which will be limited to web-based electronic databases to ensure that no personal privacy information is disclosed.

### Plans for collection, laboratory evaluation, and storage of biological specimens for genetic or molecular analysis in this trial/future use {33}

This item is not applicable. No samples will be collected.

## Statistical methods

### Statistical methods for primary and secondary outcomes {20a}

Statistical analysis will be conducted using IBM SPSS Statistics (version 22.0). Descriptive analysis will be performed for all of our variates. The analysis set will consist of the intention-to-treat (ITT) set, per protocol (PP) set, and safety set. All subjects will be included in the ITT set after randomization regardless of whether they received the treatment or not. Subjects who complete treatment sessions (M 0 to M 7) without any major violation to the trial procedure will be included in the PP set. Participants who receive treatment will be included in the safety set for safety analysis. The significance level will be set so that *P* < 0.05 will be considered significant.

The primary endpoint of this study is the change in AHI from M 0 to M 7. Intergroup comparisons will be performed using an analysis of covariance (ANCOVA) to adjust for gender, obesity status, and baseline AHI. The outcomes will be mainly analyzed using the PP set. Linear regression will be used to evaluate the correlation between observed differences of AHI and the potential prognostic factors, such as gender, BMI, neck size, and research site.

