### Trial design {8}

This study will be a multicenter and randomized controlled pilot trial. Clinical research coordinators will explain the purpose and the procedure of this study to potential subjects. The participants will undergo a series of medical tests, which will include physical examinations, maxillofacial radiography, and polysomnography, to verify the diagnosis of OSAHS and malocclusion. Subjects will be randomly divided into one of four groups—the drug treatment group, the surgical treatment group, the orthodontic treatment group, or the surgery and postoperative orthodontic group—at a ratio of 1:1:1:1. Regardless of group assignment, tests will be conducted on each group before the treatment (M 0), 7 months after the treatment (M 7), 12 months after the treatment (M 12), and 24 months after the treatment (M 24). Figure 1 shows the flow chart of the research, and Table 1 shows the clinical trial schedule.

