## Oversight and monitoring

### Composition of the coordinating center and trial steering committee {5d}

The monitor team will visit every study site biannually to ascertain that all aspects of the program are being followed and that the trial is being carried out in accordance with the provisions of the drug clinical trial quality management practices (GCP). There are three research centers in the study. Each research center includes at least three main investigators and one coordinator. Clinical research coordinators will be responsible for registering information, obtaining informed consent, and keeping in contact with participants to inform them about treatment procedures. The investigators are experienced doctors who will perform examinations and interventions for the patients. A supervisory team of three experienced doctors will be established to assess and manage the adverse events. The data processing team includes two orthodontists who will perform the localization and UA measurements and three statisticians.

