This study protocol still faces several limitations and challenges. The first is the challenge of sample selection of children with mild OSAHS and mandibular retrognathia. Due to the limited acceptance of randomization, it may take a long time to collect the sample size required for this study. The second is the challenge of subjects’ compliance. Additional services will be provided for participants through WeChat or phone to arrange treatment times and enhance adherence. The third limitation is the consistency of treatment. Before the study begins, all of the surgical and orthodontic treatment teams will receive specific training on the normalized research procedure to ensure consistency.

The results of this study will provide valuable evidence for the merits and long-term efficacy of different treatment approaches and contribute to facilitating the multidisciplinary treatment of pediatric OSAHS.

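### Site is listed as potentially prognostic but is left out of both the minimisation and the primary ANCOVA; adding it to the model is a nearly free, probably modest gain in precision and balance

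*Protocol article*

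**What the plan says.** The trial is multicentre (Trial design {8}), and the section on the coordinating center {5d} says "There are three research centers in the study". Implementation {16c} allocates "using the minimization method with 80% allocation probability according to the following stratification factors", and the two factors it lists are "1) male/female patient; (2) obese or not based on BMI". Site is not among them.

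Statistical methods {20a} compares the groups on AHI change from M 0 to M 7 by ANCOVA, "to adjust for gender, obesity status, and baseline AHI". Site is not in that list either. The same paragraph makes the per-protocol set the main analysis set, then describes a separate linear regression of AHI differences on "potential prognostic factors, such as gender, BMI, neck size, and research site". It states no treatment term for that regression and gives it no part in the group comparison.

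Methods for additional analyses {20b} applies similar methods to LSaO2, upper-airway volume and the OSA-20 total, so those analyses take over the same covariate list. The Discussion adds that "The third limitation is the consistency of treatment", and answers it with training of the surgical and orthodontic teams.

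**The concern.** Both the balancing factors and the primary covariates are given as explicit lists, so this is a choice the protocol makes and not a detail left for later. The authors place site beside gender as potentially prognostic, yet adjust for gender and not for site.

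If the hospitals differ in ways that affect all arms alike, for example in case mix, two things follow. The between-hospital variation stays in the error term and widens the confidence intervals. And where the arms happen to draw different shares of children from each hospital, part of the hospital difference passes into the treatment contrast, because neither allocation nor model removes it.

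The per-protocol emphasis adds to this. That set drops children after randomisation. If completion or major violations differ by hospital and arm, the site imbalance in the analysed set need not be chance alone.

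**Working it through.** **Inputs from the protocol.** Three hospitals; 1:1:1:1 allocation; minimisation with probability 0.8 on sex and obesity; 80 evaluable per group; effect value 0.4; power 80%; 5% significance; 352 in total (Sample size {14}).

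**Assumptions, since the protocol gives no figure.** Site explains R² = 1% to 15% of residual variance. Site shares are equal thirds or 50/30/20%. 20% of children are obese. A site shift is 0.2 to 0.5 SD. The effect value 0.4 is a standardised difference between two groups, on the residual scale of the ANCOVA as planned.

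**1. The plan's own figure.** The number per group is n = 2(z_α + z_β)²/d².
- One-sided 5%: 2(1.645 + 0.842)²/0.16 gives 78. Power at 80 is Φ(0.4·√40 − 1.645) = Φ(0.885) = 81.2%. This reproduces the stated 80.
- Two-sided 5%: 2(1.960 + 0.842)²/0.16 gives 99. Power at 80 is Φ(0.4·√40 − 1.960) = Φ(0.570) = 71.6%.
- Total: 4 × 80 × 1.10 = 352.

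The protocol does not state sidedness, so both are carried forward.

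**2. Precision.** Adjusting for site multiplies residual variance by (1 − R²), so d becomes 0.4/√(1 − R²). Leaving site out is equivalent to running the site-adjusted analysis on 80(1 − R²) per group.

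| R² (assumed) | Equivalent n without site | Two-sided power with site (71.6% without) | One-sided power with site (81.2% without) |
|---|---|---|---|
| 1% | 79.2 | 72.0% | 81.5% |
| 2% | 78.4 | 72.4% | 81.9% |
| 5% | 76.0 | 73.7% | 82.9% |
| 10% | 72.0 | 76.0% | 84.7% |
| 15% | 68.0 | 78.3% | 86.4% |

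The gain is 0.4 to 6.7 points two-sided and 0.3 to 5.2 points one-sided.

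**3. Imbalance.** The stated minimisation was simulated 300 times per scenario with N = 352. Without site as a factor, two given arms differ in one hospital's share by a median of 5 to 6 percentage points, and by 14 to 15 points at the 95th percentile. A hand check with 352/4 = 88 per arm and a share of one third agrees: SD of the difference = √(2 × ⅓ × ⅔ / 88) = 0.071, and 1.96 × 0.071 = 0.139.

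The shift in the contrast is the share gap times the site shift. At a 14-point gap:
- 0.14 × 0.2 = 0.028 SD, which is 7% of 0.4.
- 0.14 × 0.5 = 0.07 SD, which is 17.5% of 0.4.

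These figures sit near the 95th percentile of imbalance. At the median gap they are well under half as large.

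**4. Cost in degrees of freedom.** With 320 evaluable children, the planned model leaves 320 − 1 (intercept) − 3 (arms) − 3 (covariates) = 313 residual df. Three-level site leaves 311.

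**The case against.** The strongest reply is that nothing here is invalid. The ANCOVA contains both minimisation factors plus baseline AHI, so model and allocation match. Chance imbalance on an unlisted factor is already reflected in the standard error. This stands: a reader might infer that the primary estimate is biased or its type I error inflated, and for the randomised set neither follows.

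The size is also unknown. No site variance is given, the cohort is restricted to mild disease and baseline AHI is already adjusted for. At 1% to 2% the gain is negligible. This stands too.

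Three further readings go beyond the text:
- *That the protocol establishes site as prognostic.* It says only potential, in a regression meant to examine the question. Neck size is in the same list and is also outside the ANCOVA.
- *That differing surgical or orthodontic skill justifies the site term.* Skill acts only in the arms that receive those procedures, so it is mainly a treatment-by-site interaction, which an additive term does not remove. The protocol also requires at least 5 years' experience and training in standardised procedures (Intervention description {11a}). Nor does it say who scores the polysomnograms, so local scoring differences are conjecture. Upper-airway CBCT is done at one hospital and measured by two trained analysts blinded to patient information, so for that endpoint the argument rests on case mix.
- *That the minimisation must now be changed.* Recruitment has run since May 2018 (Trial status). A change would need sponsor and Ethics Committee agreement and a new signed version ({25}). Balancing within site could also make allocations easier for site staff to guess. That is a trade-off, not a correction.

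What the reply does not answer is why a three-level factor that the authors themselves think may matter should stay out of the main comparison when including it costs almost nothing. The separate regression does not supply the adjustment.

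**Conclusion.** The point holds as a low-cost improvement to a covariate list that the protocol states. Site is absent from both allocation and primary model, and its one appearance does nothing for the treatment contrast. The consequences are lost precision and uncorrected additive site differences in the realised comparison, mainly per protocol.

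The size depends wholly on the assumed site variance. The benefit may be trivial or may reach several power points, and the contrast shift of up to 0.07 SD needs both an unusually large imbalance and a 0.5 SD site shift. The site term would also remove only the additive part of any imbalance created by per-protocol exclusions; it does not make that set equivalent to the randomised one.

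**What to change.** Before outcomes are analysed, add study site as a three-level fixed effect to the primary ANCOVA, in both the intention-to-treat and per-protocol analyses. The model would then contain treatment group, sex, obesity status, site and baseline AHI. Make the same addition to the analogous models for LSaO2, upper-airway volume and the OSA-20 total. Justify the term by differences common to all arms, such as case mix, and not by operator skill. Record the change, dated, through the amendment route in {25}.

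The cost is two residual degrees of freedom (313 to 311) and a short amendment. Recruiting hospital is known for every child, so no new data are needed. No change to the minimisation is required.

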### Provisions for post-trial care {30}

Participants may quit the study at their guardians’ discretion or defer to the supervisory team if they are not responding well to treatment. They will be followed up and receive appropriate therapy free of charge after they leave the study.

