### Methods in analysis to handle protocol non-adherence and any statistical methods to handle missing data {20c}

Missing data will be dealt with using the last-observation-carried-forward (LOCF) method.

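### The main comparison of AHI change is assigned to the per-protocol set rather than the intention-to-treat set, so it can be biased in either direction if exclusions differ by arm and relate to outcome

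*Protocol article*

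**What the plan says.** Under Statistical methods for primary and secondary outcomes {20a}, the protocol article defines three analysis sets: ITT, PP and safety.

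- On the ITT set: "All subjects will be included in the ITT set after randomization regardless of whether they received the treatment or not".
- On the PP set: "Subjects who complete treatment sessions (M 0 to M 7) without any major violation to the trial procedure will be included in the PP set".
- On the endpoint and method: "The primary endpoint of this study is the change in AHI from M 0 to M 7", and "Intergroup comparisons will be performed using an analysis of covariance (ANCOVA) to adjust for gender, obesity status, and baseline AHI".
- The next sentence sets the priority: "The outcomes will be mainly analyzed using the PP set".

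No section gives the ITT set a primary or co-primary role for AHI. Methods for additional analyses {20b} extends similar methods to LSaO2, upper-airway (UA) volume and the OSA-20 total score.

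On missing data, section {20c} says: "Missing data will be dealt with using the last-observation-carried-forward (LOCF) method".

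On leaving the trial, Provisions for post-trial care {30} lets families withdraw a child or "defer to the supervisory team if they are not responding well to treatment".

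**The concern.** The hypothesis in Sample size {14} is that treatment lowers AHI, and the trial is sized to detect a difference. No non-inferiority or equivalence margin appears, so the usual reason for giving weight to a PP analysis is absent.

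Three features make the choice risky here.

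1. PP membership depends on events after randomisation, namely completion and major violations.
2. Completion means different things by arm under Intervention description {11a}: a daily spray for two months, one operation, a removable appliance, or an operation followed by the appliance.
3. Leaving can be linked to poor response, under section {30}.

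Children retained in one arm may therefore differ in prognosis from those retained in another. Part of the observed difference in AHI change would then reflect who was kept and not what the treatment did. Randomisation does not protect against this, and the three covariates in the ANCOVA remove only the part of the imbalance that they explain.

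**Working it through.** **The plan's own figure.** Sample size {14} gives 80 per group, an effect value of 0.4, 80% power, a 5% level and about 10% dropout. 80 × 1.10 = 88 per arm, and 4 × 88 = 352, as stated. Taking 0.4 as a standardised difference between two arms (the article does not define it), 80 per group gives 81.2% power one-sided and 71.6% two-sided. Only the one-sided reading reproduces 80%.

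**Inputs to the illustration.** From the document: 88 randomised per arm. Assumed, because the document gives no values: exclusion proportions e1 and e2 in two arms, and a gap of k SD by which excluded children do worse than retained ones. There is no true treatment effect, the outcome SD is 1, and the test is an unadjusted two-sided 5% normal test.

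**Bias.** In each arm, the mean of all randomised children equals the retained mean minus e × k, where a higher value is a better outcome. With no true effect the full-arm means are equal, so

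spurious PP difference = k × (e2 − e1).

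**Type I error.** With n1 = 88(1 − e1), n2 = 88(1 − e2), SE = √(1/n1 + 1/n2) and z = bias/SE,

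type I error = 1 − Φ(1.96 − z) + Φ(−1.96 − z).

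| e1 vs e2 | k (SD) | n1, n2 | Bias (SD) | SE | z | Type I error |
|---|---|---|---|---|---|---|
| 5% vs 15% | 0.3 | 83.6, 74.8 | 0.030 | 0.159 | 0.19 | 5.4% |
| 5% vs 25% | 0.5 | 83.6, 66.0 | 0.100 | 0.165 | 0.61 | 9.3% |
| 5% vs 40% | 0.5 | 83.6, 52.8 | 0.175 | 0.176 | 1.00 | 16.9% |

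**When it does not matter.** If e1 = e2, the bias is zero for any k. With 5% against 10% excluded, type I error runs only from 5.1% (k = 0.25) to 6.2% (k = 1).

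**What changing the set does to N and power.** N stays at 352. With all 88 per arm analysed and an effect of 0.4, power is 84.3% one-sided or 75.6% two-sided. If non-adherence diluted the effect by 10% to 0.36 (assumed), it would be 77.1% or 66.6%.

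**Interaction with LOCF.** In Table 1 the polysomnogram is scheduled at baseline, M 7, M 12 and M 24. M 7 is the first after baseline, so for a child with no M 7 recording the only earlier scheduled value is baseline. Carrying it forward gives a change of exactly zero. The PP rule, which requires completion to M 7, largely hides this. An ITT analysis would expose it.

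**The case against.** The strongest reply is that the harm is conditional and the document does not show that the conditions are met.

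- **Size.** The only attrition figure is about 10% dropout overall. Dropout is not the same as PP exclusion, but nothing in the article supports 25% or 40% in an arm. At exclusion rates near 10% the inflation is negligible. This stands: a reader might infer that the type I error is certainly no longer 5%, and the documents do not support that.
- **Direction.** A reader might infer that nearly all surgical children would stay in the PP set while appliance wearers are filtered. The article does not say so. Its Discussion warns of limited acceptance of randomisation, and surgery under general anaesthesia could be declined after allocation, so the imbalance could be absent or reversed. This also stands.
- **Appliance duration.** At least seven months of appliance wear might be inferred from the PP window, but no orthodontic duration is stated.
- **Response-related leaving.** Section {30} applies to every arm. It distorts the contrast only if leaving differs between arms.
- **Method.** The planned four-group ANCOVA would absorb whatever part of the completer gap is explained by baseline AHI, gender and obesity status. The illustration is cruder than the planned analysis.
- **ITT is not absent.** The set is defined, and the word mainly leaves room for an ITT analysis. The fault is the order of priority, not the loss of any randomised comparison from the trial.
- **Pilot label and objective endpoint.** Trial design {8} calls this a pilot, and attended polysomnography is an objective measure. Neither helps: the trial is sized for efficacy at 80% power, and selection into the PP set does not depend on how AHI is measured.

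These points limit the size and remove any claim about direction. None is a positive reason to prefer PP for a difference hypothesis.

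**Conclusion.** The concern holds as a fault in the stated priority of analysis sets. The PP set is named as the main set for a comparison of difference, with ITT given no primary role. The result can be biased either way if exclusions differ by arm and relate to outcome.

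Under the labelled assumptions, type I error ranges from about 5.4% to about 17% in the three scenarios shown, and it stays close to 5% if exclusions are few or balanced. The documents do not establish that inflation will occur, how large it would be, or which arm would gain. The case for change is that the ITT comparison does not rely on exclusions being balanced, which the protocol cannot guarantee. The Discussion itself names compliance as a challenge.

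Changing the set alone is not enough. Under the stated LOCF rule, an ITT analysis would score children missing M 7 as unchanged, and with unequal dropout that could itself bias the contrast.

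**What to change.** Replace the sentence on the main analysis set with: *The primary analysis of AHI change from M 0 to M 7 uses the ITT set, with children analysed in the arm to which they were randomised; the PP analysis is supportive.* Apply the same rule to LSaO2, UA volume and the OSA-20 total score.

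In the same edit, replace LOCF for a missing M 7 value with multiple imputation, or with a mixed model for repeated measures using baseline, M 7, M 12 and M 24. Both rest on a missing-at-random assumption, which should be stated. Keep LOCF at most as a sensitivity analysis.

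Cost: the ITT set is already defined and N stays at 352. There is a little more analysis work, and the estimated effect may be smaller than in completers. The change should be made and dated before outcome data are compared by arm, because a later switch of primary set would look data-driven.
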